### Selection and randomization of subjects

Male participants, 18–50 years of age, who present to the orthopedic surgeon with recent knee trauma will be screened for eligibility. Eligible patients will have had rotational trauma to a previously uninjured knee within the preceding 8 months, ACL insufficiency as determined by clinical examination (positive pivot shift and/or positive Lachmann test), and a score of 5 to 9 on the Tegner Activity Scale (TAS) [12] before the injury (scores range from 1 to 10, with a score of 5 indicating participation in recreation sports, and a score of 9 indicating participation in competitive sports on a nonprofessional level).

All eligible participants (see Table 1) will receive information about the trial orally and in writing. After signing a written informed consent, they will be randomly assigned to undergo either standard-of-care structured rehabilitation with testosterone administration or standard-of-care structured rehabilitation with placebo. An investigator not involved in the randomization procedure will prepare sequentially numbered, opaque, sealed envelopes containing the assigned interventions to ensure randomness which will then be provided to the research pharmacist. The study is a double blind study. Only the research pharmacist will know which patient is receiving study drug or placebo. The surgeon, PI, study team, and physical therapist will not know which study arm the patient was randomized. The protocol for rehabilitation will remain the same for all patients.

**Table 1 Tab1:** **Inclusion and exclusion criteria**

Inclusion criteria	Exclusion criteria
Eligible participants will have had:	• Previous major knee injury or knee surgery
• A complete ACL tear as visualized on MRI	• Associated posterior cruciate ligament (PCL) or medical collateral ligament (MCL) injury grade III
° The ACL injury can be either “isolated” or combined with one or several of the following injuries visualized on MRI and/or arthroscopy:	• Concomitant severe injury to contra-lateral knee
▪ A meniscus tear that is either left untreated or treated with a partial resection	• Injury to the lateral/posterolateral ligament complex with significantly increased laxity
▪ A small, stable meniscus tear treated with fixation, but with the fixation not interfering with the rehabilitation protocol	• Unstable longitudinal meniscus tear that requires repair and where the following postoperative treatment (e.g. bracing and limited range of motion) interferes with the rehabilitation protocol
▪ Cartilage changes verified on MRI with an arthroscopically determined intact surface.	• Bi-compartmental extensive meniscus resections
• A radiographic examination with normal joint status or combined with either one of the following findings:	• Cartilage injury representing a full thickness loss down to bone
° A small-avulsed fragment located laterally, usually described as a Segond fracture, JSN grade 1 or osteophytes grade 1 as determined by the OARSI atlas[15]	• Total rupture of MCL/LCL as visualized on MRI.
	• History of deep vein thrombosis (DVT) or a disorder of the coagulative system
	• Claustrophobia
	• Prior or current use of anabolic steroids
	• General systemic disease affecting physical function
	• Chromosomal disorders
	• Medications that interfere with testosterone production or function, including but not limited to 5α-reductase inhibitors
	• Any other condition or treatment interfering with the completion of the trial

### Study agent administration and safety

Although the study involves a very short course of testosterone, it may still have side effects on the endocrine systems; and therefore, common markers of endocrine function are monitored. Blood analysis will be performed at USC. Pituitary hormones (LH and FSH), prostate-specific antigen (PSA), liver enzymes, hematocrit, and blood pressure are measured at two weeks preoperatively, 1 day preoperatively, and 2, 3, 6, 12, and 24 weeks postoperatively.

### Orthopedic surgery

Surgery will be performed for all eligible patients within 8 months after the injury by a licensed orthopedic surgeon. Surgery will be performed while the patient is under general anesthesia. Meniscal surgery will be carried out as needed, followed by ACL reconstruction. All surgeons have similar success rates for ACL reconstruction.

### Rehabilitation

Rehabilitation will follow a standard guideline [16] under the supervision of a licensed physical therapist and the participant’s doctor.

### Muscle biopsies

During surgery, vastus lateralis muscle tissue will be obtained. The tissue will then be examined by q-PCR for changes in the gene expression of *Akt*-*1*, *mTOR*, and *FOXO3a*
[17–21]. In tissues that have received 2 weeks of testosterone, we expect to see up-regulated expression of *Akt*-*1* and *mTOR*, and down-regulated expression of *FOXO3a*. Akt-1 phosphorylation will also be detected by western blotting, and should be higher in patients receiving testosterone.

### Clinical and laboratory evaluations

The patient will be tested on multiple occasions. All testing takes place at the USC Clinical Exercise Research Center (CERC). Information will be collected 2 weeks prior to surgery, followed by measurements 1 day prior to surgery, and 2, 6, 12, and 24 weeks after surgery. Surgery will be performed on an arranged date with the orthopedic surgeon. Physical therapy will follow a pre-defined protocol with a physical therapist.

Table 2 outlines the timeline used for the study including the dates of each visit and what takes place on each visit.

**Table 2 Tab2:** **Study calendar**

Timeline	Drug delivery	Blood collection	BC testing	PF testing	Questionnaires
2 weeks prior to surgery	X	X	X	X	X
1 week prior to surgery	X				
1 day prior to surgery	X	X	X	X	X
1 week post-surgery	X				
2 weeks post-surgery	X	X			
3 weeks post-surgery	X				
4 weeks post-surgery	X				
5 weeks post-surgery	X				
6 weeks post-surgery		X	X	X	X
12 weeks post-surgery		X	X	X	X
24 weeks post-surgery		X	X	X	X

BC = Body Composition, PF = Physical function.

#### Drug delivery

Either testosterone or placebo will be injected intramuscularly once per week for 8 weeks, starting 2 weeks prior to surgery and ending 5 weeks post-surgery.

#### Blood draw

Blood will be collected to monitor any adverse effects on the participant’s health.

#### Body composition testing by bioelectrical impedance

The Biospace InBody 520 [22] device measures body composition as the participant stands on a scale-like device while grasping two handles; one in each hand. The device works by sending a very low-voltage electrical signal through the body to determine water content, body fat percentage, and lean (muscle) mass.

#### Body composition testing by DXA

We will also measure the participant’s lean mass and body fat percentage by whole-body dual-energy x-ray absorptiometry [22–24] (DXA), which is more sensitive to small changes in body composition than bioelectrical impedance. The subject will have DXA scans throughout the study. The DXA works by passing low energy x-rays through the subject’s body. The x-ray is absorbed differently by muscle tissue than fat tissue which allows the device to differentiate the amount of lean mass and fat mass in the participant’s body.

#### Physical function tests

At 2 weeks prior to surgery, 1 day prior to surgery, and 6, 12, and 24 weeks after surgery, tests of maximal muscle strength using a Cybex dynamometer [25–27] will be performed on the subject’s unaffected and affected leg. In addition, knee stability and flexibility tests of the affected leg are typically performed during rehabilitation. During later stages of rehabilitation, tests may include the single leg squat, single leg hop, X-hop, triple hop, and timed hop tests [19, 28–31].

#### Questionnaires

The subject will be asked to complete the Knee Injury and Osteoarthritis Outcome Score [32, 33] (KOOS), a commonly used test to measure progression after ACL reconstruction, and the Tegner Activity Scale [12, 34–37] to determine physical activity level.

### Statistical data analysis

Descriptive statistics will be performed for participant characteristics as well as baseline testosterone, strength, and body composition. Comparisons across groups will be made for each measurement (t-test) to determine if bias exists between the randomized groups. If bias does exist, these variables will be included as covariates in the primary analysis. The raw data (pre- and post-test) will be plotted to determine if outliers exist. Because the sample size is small if outliers are found, transformations of the data (e.g. log transformation) will be attempted. If this is not feasible, results will be compared using non-parametric analogs to the parametric tests listed below. Intent to treat analyses for specific hypotheses are listed below. In addition, effect sizes will be computed with Cohen’s D to determine the clinical relevance of the results and assist in powering further research. Analyses will be performed using SPSS for all analyses with α = 0.05. If there is any missing data, the analyses can be performed with the SPSS multiple imputation procedure.

Intent to treat will be tested by comparing changes in lean mass and strength using ANCOVA models, with group adjusting for baseline values. KOOS and TAS scores will be analyzed by ANCOVA models. Physical function tests scores on the Lachman and pivot shift tests will be analyzed by χ^2^ test. The changes in gene expression of *Akt1*, *mTOR*, and *FOXO3a* will be compared by ANCOVA models.

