#### Power analysis

Sample size estimates were computed with Nquery (v4) for α = 0.05 and 1-β = 0.80. Preliminary data was taken from a study that provided 12 weeks of oxandrolone/day in 32 healthy 60–87 year old men [24]. Effects sizes between changes in means from baseline to 12 weeks for lean body mass and maximal voluntary strength were used to estimate the changes in mass and strength for Aim 1. The effect size was 2.0 for mass and 2.03 for strength. For similar effects, a minimum of 6 men would be needed for each group. Assuming a 20% attrition rate [1] and similarly very large effect, our sample of 7 per group should be sufficient to see statistically significant effects.

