### Limitations

Testosterone therapy is currently a controversial topic but previous studies have shown positive results [8, 41–48]. It may have been ideal to personalize the supraphysiologic doses according to baseline for each participant. However, for ease of administration and future research viability, we attempted to standardize this value. It may be interesting to note variability of the peak testosterone values and results for those participants. Similarly, there is a large age range of participants and studies have shown differences in testosterone level as early as 40 years of age [44, 48–52]. However, additional studies show that the effects in males will still exist with supraphysiologic doses [48, 53, 54] and we expect an effect to be measured independent of age or race.

Recruitment of participants who meet all inclusion criteria will be challenging. Although we are working with multiple orthopedic surgeons, there are a number of challenges in recruiting patients with ACL injury into randomized clinical trials [55]. It will likely be necessary to recruit and screen approximately 70 participants -- 5 times as many potential participants as our power analysis indicates to demonstrate significant differences.

Additionally, while we aim to work with as few physical therapists as possible and are following a standardized protocol, there are differences in the techniques and progression of individual therapists. We intend to monitor progress of individual participants as standardized as possible and to also focus on the 24 week result as the primary outcome time point.

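### Additional covariates enter the primary analysis only when a baseline t-test between randomised arms is significant; with 7 per arm this selects on chance imbalance and costs some power

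*Protocol article*

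**What the plan says.** All the relevant text is in the article's Statistical data analysis section.

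- **What is described at baseline:** "Descriptive statistics will be performed for participant characteristics as well as baseline testosterone, strength, and body composition". The participant characteristics are not listed.
- **The test:** "Comparisons across groups will be made for each measurement (t-test) to determine if bias exists between the randomized groups".
- **The consequence:** "If bias does exist, these variables will be included as covariates in the primary analysis". No other criterion for bias is given. The section also says "Analyses will be performed using SPSS for all analyses with α = 0.05", so p < 0.05 is the natural reading. Sidedness is not stated; I take it as two-sided.
- **What is fixed regardless:** the main analysis consists of "comparing changes in lean mass and strength using ANCOVA models, with group adjusting for baseline values". The own baseline is therefore in the lean mass and strength models whatever the t-tests show.
- **What is not fixed:** "KOOS and TAS scores will be analyzed by ANCOVA models", with no covariate named.

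The Power analysis section plans on effect sizes of 2.0 (mass) and 2.03 (strength), with a minimum of 6 men per group and 7 enrolled per group.

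**The concern.** If allocation is random, any baseline difference between the arms is chance. A significance test cannot reveal bias in that setting; it can only pick out the larger chance differences. Used to choose covariates, it has three faults:

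1. **It is insensitive at this size.** Substantial imbalances go unflagged.
2. **It asks the wrong question.** A covariate earns its place by predicting the outcome, not by differing between arms.
3. **It favours awkward covariates.** A flagged variable is correlated with treatment by construction. Adding it inflates the standard error of the treatment effect and uses a residual degree of freedom, of which there are only 11 with 14 men, group and own baseline in the model.

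At stake are the precision of the lean mass and strength comparisons and a primary model that is not known until the baseline data have been seen.

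**Working it through.** **Inputs from the article:** 7 per arm, minimum 6 per arm, effect sizes 2.0 and 2.03, α = 0.05, power 0.80. **Assumptions, because the article gives none:** number of screened variables, their independence, and the correlations of the outcome with its own baseline and with one extra covariate.

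**1. The plan's own sample size.** Two-sample t-test, two-sided 0.05, noncentral t. At d = 2.0, power is 79.0% with 5 per group and 87.6% with 6, so the stated minimum of 6 is reproduced. With 7 per group it is 92.9%.

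**2. Smallest gap that is flagged.** This is t(0.975, 2n−2) × √(2/n), in pooled SDs.
- n = 7: 2.179 × 0.5345 = 1.16 SD
- n = 6: 2.228 × 0.5774 = 1.29 SD

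Randomisation alone gives a gap of at least 0.8 SD on a given variable with probability 2[1 − Φ(0.8/0.5345)] = 13% at 7 per arm. In simulation about 65% of those gaps are not flagged, and about 42% of gaps of at least 1.0 SD.

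**3. Chance flags.** With k independent variables, P(at least one) = 1 − 0.95^k: 14% for k = 3, 19% for k = 4, 26% for k = 6.

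**4. Overlap with treatment at the threshold.** R² = t²/(t² + df); the standard error is multiplied by 1/√(1 − R²).
- n = 7: 4.75/16.75 = 0.28, so about 18% larger
- n = 6: 4.96/14.96 = 0.33, so about 22% larger

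Only a sufficiently prognostic variable offsets this.

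**5. Power at the planned effect, d = 2.0.** Simulation, 40,000 trials per setting, 4 screened variables. Correlations are own baseline / extra covariate.

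| Per arm | Correlations | Own baseline only | Stated rule | Own baseline + one fixed covariate |
|---|---|---|---|---|
| 7 | 0.3 / 0 | 92.4% | 89.0% | 89.1% |
| 7 | 0.3 / 0.3 | 92.2% | 89.2% | 91.7% |
| 7 | 0.5 / 0.5 | 96.0% | 94.2% | 98.6% |
| 7 | 0.3 / 0.7 | 92.2% | 90.5% | 99.3% |
| 6 | 0.3 / 0 | 85.9% | 81.4% | 80.6% |
| 6 | 0.5 / 0.5 | 91.4% | 88.1% | 95.8% |

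With 6 screened variables and correlations 0.3 / 0.3, own-baseline-only against the rule is 92% against 87% at 7 per arm, and 86% against 79% at 6 per arm. In the roughly 26% of trials where something is flagged, power under the rule is about 74% at 7 per arm and about 60% at 6 per arm.

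**6. Type I error under the rule:** 3.5% to 5.1% across the settings tried.

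**The case against.** The best defence is that the damage is limited, and much of it stands.

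- A reader might infer that every covariate, including the outcome's own baseline, depends on the t-test. The text does not say that: own-baseline adjustment is unconditional for lean mass and strength, and it is probably the most useful covariate.
- A reader might infer that the primary p-value is invalid. The simulations show no inflation of type I error.
- A reader might expect a dramatic loss of power. At an effect of 1 SD, with a covariate known in advance to correlate 0.5 with the outcome, the rule gives 44.8% against 59.1% for the fixed model (own-baseline correlation 0.5, 4 screened variables). But the article plans on effects of about 2, and nothing in it supports that correlation. Against a fixed covariate that is not prognostic, the rule loses nothing with 4 screened variables (89.0% against 89.1%).
- Calling a flagged variable highly collinear with treatment would overstate an R² of 0.28 at the threshold. More extreme flags overlap more.
- The chance-flag rates assume independent variables. Strength and body composition measures are unlikely to be independent, and the number tested is not stated.

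The defence does not justify the rule itself. With a true effect, it had lower power than own-baseline-only ANCOVA in every setting tried, and it gives no type I benefit in return. Nor is this a detail left to an unseen analysis plan: the article states the rule outright.

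**Conclusion.** The concern holds for additional covariates, and for KOOS and TAS, where no fixed covariate is named. The test cannot show bias between properly randomised arms, it overlooks gaps below 1.16 SD at 7 per arm, and it selects on imbalance instead of prognosis. At the planned effect the cost is roughly 1 to 5 points of power at 7 per arm and up to about 7 points at 6 completers per arm, where it can bring power just below the planned 80%. These sizes rest on 4 to 6 independent screened variables, the assumed correlations, and p < 0.05 as the meaning of bias. The documents do not support a claim of false-positive inflation or of an invalid primary analysis. This is a should-fix point.

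**What to change.** 1. Delete the baseline t-tests and the sentence that makes covariates conditional on them.
2. State the primary model for lean mass and strength as ANCOVA with group and the outcome's own baseline, and nothing else by default. Name the own baseline as the covariate for KOOS and TAS as well.
3. Present baseline data descriptively by arm, without p-values.
4. Treat any further covariate as optional. If one is wanted, name it in advance on prognostic grounds and use it whatever the observed imbalance.

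Age is not an obvious choice for step 4. The Limitations section notes that "there is a large age range of participants and studies have shown differences in testosterone level as early as 40 years of age", but goes on to expect an effect that does not depend on age.

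Steps 1 to 3 cost a few sentences and no patients. Step 4 costs one residual degree of freedom and, if the covariate proves non-prognostic, about 3 points of power at 7 per arm (92.4% to 89.1%).

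### Covariates beyond the outcome's own baseline are chosen by baseline t-tests between randomised groups, so chance rather than prognosis decides what enters the primary model

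*Protocol article*

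**What the plan says.** All of this stands in the Protocol article, Statistical data analysis.

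- The baseline variables are listed: "Descriptive statistics will be performed for participant characteristics as well as baseline testosterone, strength, and body composition".
- They are then tested: "Comparisons across groups will be made for each measurement (t-test) to determine if bias exists between the randomized groups".
- The result decides the model: "If bias does exist, these variables will be included as covariates in the primary analysis".
- The next paragraph describes the main analysis as "comparing changes in lean mass and strength using ANCOVA models, with group adjusting for baseline values". No condition is attached, so the outcome's own baseline is always in the model for lean mass and strength.
- KOOS and TAS are also assigned to ANCOVA, but no covariate is named for them.
- A separate rule on outliers reads: "Because the sample size is small if outliers are found, transformations of the data (e.g. log transformation) will be attempted". If transformation is not feasible, non-parametric analogues replace the parametric tests.

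Baseline strength and body composition are therefore conditional covariates under the first paragraph and unconditional ones under the second.

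**The concern.** The rule treats a significant baseline difference as evidence of bias. With concealed random allocation (sealed envelopes, as Selection and randomization of subjects describes), any such difference is due to chance. The t-test asks whether the groups differ on a variable. Adjustment is worthwhile if the variable predicts the outcome, and the test does not address that.

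The rule can go wrong in two ways:

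1. A variable that is flagged is, because it was flagged, correlated with treatment group. Putting it in the model spends information on separating the two, and unless it is prognostic nothing is gained in return.
2. A prognostic variable with a sizeable but non-significant imbalance is left out. With about 7 men per arm that is the usual case.

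The primary model is thus unknown until the baseline data have been tested. The outlier rule adds a second data-dependent step, because the scale and possibly the test are settled after the pre- and post-test data have been plotted.

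**Working it through.** **Inputs from the article.** 7 per group, 20% attrition and effect sizes of 2.0 and 2.03 on changes (Power analysis); alpha 0.05 (Statistical data analysis). **Assumed.** The threshold for the baseline t-test is 0.05, two-sided, because only a general alpha is given. The number of variables tested and all correlations with outcome are also assumptions; the article gives neither.

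**The plan's own figure.** Two-sided two-sample t-test, noncentral t. At d = 2.0, power is 79.0% with 5 per group and 87.6% with 6. At d = 2.03 it is 80.2% and 88.6%. The stated minimum of 6 is reproduced and does not depend on the covariate rule.

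**Cost of a flagged variable.** At the threshold, the squared correlation of the variable with group is r² = t²/(t² + df), and the variance factor is 1/(1 − r²).

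| Per arm | df | t | r² | Variance factor | SE factor |
|---|---|---|---|---|---|
| 7 | 12 | 2.179 | 0.283 | 1.40 | 1.18 |
| 5 | 8 | 2.306 | 0.399 | 1.66 | 1.29 |

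The row for 5 is shown because 7 × 0.80 = 5.6 men per arm would remain after the stated attrition. These are minimum values, since a larger t gives a larger factor. They apply to a variable with no prognostic value.

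**What is never flagged.** The smallest observed difference that reaches significance is t × √(2/n) = 2.179 × √(2/7) = 1.165 pooled SD. An observed imbalance of exactly 1 pooled SD gives t = 1/√(2/7) = 1.87, below 2.179.

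**How often something is flagged.** With k independent variables the chance is 1 − 0.95^k: 14.3% for 3, 22.6% for 5, 33.7% for 8.

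**Simulation A: irrelevant variables.** 7 per arm, 20,000 trials per setting, own baseline always in the model with correlation 0.7 to outcome, all other tested variables unrelated to outcome. An effect of 2.0 on the change scale equals 2.0 × √(2 × (1 − 0.7)) = 1.55 outcome SD.

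| Variables tested | Power at 1.2 SD: no rule → rule | Power at 1.55 SD: no rule → rule |
|---|---|---|
| 5 | 78% → 73% | 94% → 90% |
| 8 | 78% → 70% | 94% → 87% |

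A separate run of 8,000 trials at 1.2 SD gave 78% → 74% and 77% → 69%. When at least one variable was flagged, the SE rose on average by a factor of about 1.31 (5 variables) or 1.34 (8). Type I error stayed near 5%.

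**Simulation B: one further covariate.** 7 per arm, 200,000 trials per setting, own baseline always in the model (correlation 0.3 to outcome). The covariate enters only if flagged, or always.

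| Covariate–outcome correlation | SD of estimate: if flagged / always | Power at d = 1.0 | Power at d = 2.0 | Type I error |
|---|---|---|---|---|
| 0 | 0.544 / 0.564 | 39.8% / 37.1% | 91.5% / 89.1% | 5.0% / 5.0% |
| 0.3 | 0.537 / 0.535 | 39.8% / 40.4% | 91.7% / 91.7% | 4.8% / 5.0% |
| 0.5 | 0.523 / 0.480 | 39.9% / 48.0% | 92.4% / 95.9% | 4.4% / 5.1% |
| 0.7 | 0.507 / 0.384 | 40.5% / 66.4% | 93.1% / 99.4% | 3.8% / 5.0% |

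Against naming the covariate in advance, the rule makes the SD of the estimate 9% larger at correlation 0.5 (0.523/0.480) and 32% larger at 0.7 (0.507/0.384). At 0.3 there is almost no difference. At 0 the rule does slightly better than always including it, though worse than leaving it out.

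**The case against.** Several stronger readings are tempting, and the article does not support them.

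- **That all adjustment hinges on the t-test.** It does not. For lean mass and strength the own baseline is in the model without condition, so the most useful covariate is already secured. This stands and limits the point to further covariates.
- **That the trial loses its power.** At the planned effect, with 7 men analysed per arm, power stayed at 87% or more in every setting above. The larger losses need a smaller effect, many irrelevant variables, or a strongly prognostic covariate left out. The article supplies none of these inputs. This stands. Whether an effect of 2.0 is realistic is a separate question.
- **That false positives increase.** They do not; type I error is about 4% to 5%.
- **That a log transformation is impossible because losses are expected.** The text speaks of raw pre- and post-test data, and raw lean mass and strength are positive. A log is offered only as an example.

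It can also be said that detailed outlier triggers may sit in a fuller plan that is not shown. That is fair, and the outlier rule is only a secondary point here, with no size attached. The covariate rule is different: the article states it outright, so it is a fixed rule and not an omission.

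**Conclusion.** The point holds for covariates beyond the outcome's own baseline. The rule mistakes chance for bias and selects on a criterion unrelated to prognosis. A flagged variable with no prognostic value costs at least 18% in SE at 7 per arm and 29% at 5. Observed imbalances below about 1.165 pooled SD are never acted on at 7 per arm.

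The damage is to precision and to having the model fixed in advance, not to the false-positive rate. The threshold figures rest only on a two-sided 0.05 level for the baseline tests. The power figures rest on assumed correlations, effects and numbers of variables, and should be read as illustrations. The change is worth making because it is cheap and the trial is very small, but the planned power calculation does not fail on this account.

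**What to change.** 1. Delete the baseline t-tests and the rule that depends on them. Keep the baseline table descriptive, without p-values.
2. State one ANCOVA per outcome with group and the outcome's own pre-treatment value, measured 2 weeks before surgery, always in the model. This is already the approach for lean mass and strength; extend it to KOOS and TAS.
3. Add no further covariate unless it is named in advance as prognostic, and then at most one.
4. Secondary: make this ANCOVA the primary result whatever the outlier plot shows. Report any transformed, rank-based or permutation analysis as a prespecified sensitivity analysis.

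The cost is analysis wording only, with no change to data collection or sample size. The downside is small: a chance imbalance in a variable that was not named stays unadjusted, which the present rule would also leave in most cases.

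### Every outcome is tested at 0.05 with no primary outcome and no leg fixed for strength, so false-positive risk is uncontrolled and a significant result need not reflect the operated limb

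*Protocol article*

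**What the plan says.** All points are from the protocol article.

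- **Error rate.** Statistical data analysis: "Analyses will be performed using SPSS for all analyses with α = 0.05". The section speaks of a primary analysis but names no primary outcome, order of testing or division of alpha.
- **Outcomes tested.** The same section lists nine: lean mass, strength, KOOS, TAS, Lachman, pivot shift and the expression of three genes. The intention-to-treat comparison is described as "comparing changes in lean mass and strength using ANCOVA models, with group adjusting for baseline values".
- **Sizing.** Power analysis: "Sample size estimates were computed with Nquery (v4) for α = 0.05 and 1-β = 0.80", and "The effect size was 2.0 for mass and 2.03 for strength". Neither outcome ranks above the other.
- **Time point.** Limitations makes 24 weeks the primary time point.
- **Lean mass.** Besides impedance, the plan measures "lean mass and body fat percentage by whole-body dual-energy x-ray absorptiometry", a method "which is more sensitive to small changes in body composition than bioelectrical impedance". No leg region is named for either device.
- **Strength.** Physical function tests has dynamometry done on the "unaffected and affected leg". The analysis section does not say which leg enters the comparison.

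**The concern.** There are two linked problems.

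First, giving 0.05 to every analysis, with no outcome named primary, leaves the chance of a false positive finding above 5%. This is already so for the two outcomes on which the trial was sized.

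Second, those two outcomes are not tied to the operated limb. Background and Use of testosterone both say that the drug raises muscle mass and strength in the absence of exercise, the latter in young healthy men like those enrolled here. A rise in total lean mass, or in strength of the uninjured leg, could therefore occur even if the operated leg wasted equally in both groups. It would still satisfy the comparison as written, while the Discussion and Conclusion are framed around recovery from ACL reconstruction.

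**Working it through.** **1. Reproduce the plan's own figure.** Inputs from Power analysis: standardised effects 2.0 and 2.03, alpha 0.05 (taken as two-sided, since the article does not say), power 0.80, stated minimum 6 per group. For a two-sample t-test the non-centrality is d × √(n/2) on 2n − 2 degrees of freedom.

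- d = 2.0, n = 5: power 0.791.
- d = 2.0, n = 6: non-centrality 2.0 × √3 = 3.46, power 0.876.
- d = 2.03, n = 5: power 0.802; n = 6: 0.886.

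Six per group is reproduced, with the full 0.05 spent on each outcome separately.

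**2. False-positive risk if the drug has no effect on any outcome.** With k independent tests at 0.05, the chance of at least one significant result is 1 − 0.95^k.

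| Outcomes counted | k | Independent |
|---|---|---|
| Lean mass and strength | 2 | 1 − 0.95² = 9.75% |
| Plus KOOS, TAS, Lachman, pivot shift | 6 | 1 − 0.95⁶ = 26.5% |
| Plus three genes | 9 | 1 − 0.95⁹ = 37.0% |

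The genes come from tissue taken at surgery, so only the first two rows concern outcomes that could be read at 24 weeks.

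**3. Allow for correlation.** The article gives no correlations, so a range is assumed. Simulated two-sided t-tests with 7 per group, equal correlation between outcomes and 100,000 runs gave:

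| Correlation | 2 outcomes | 9 outcomes |
|---|---|---|
| 0.3 | 9.5% | 33% |
| 0.5 | 9.2% | 28% |
| 0.8 | 8.0% | 18% |

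**4. Does the measurement identify the operated limb?** Setting the sections side by side: the DXA section describes a whole-body scan, the impedance section a current through the body, and the strength section both legs; the analysis section says only lean mass and strength. The sizing effects come from the same general quantities: "Effects sizes between changes in means from baseline to 12 weeks for lean body mass and maximal voluntary strength were used", in healthy older men given another anabolic agent. The muscle biopsy is taken during surgery, so it cannot show what was retained afterwards.

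**5. What a remedy does to power.** Splitting alpha equally (0.025 each) at d = 2.0 gives power 0.863, 0.781 and 0.662 with 7, 6 and 5 per group. A fixed sequence holds the overall error at 5% and leaves the first test its full power: 0.929, 0.876 and 0.791. At the plan's own effects, and if the two tests were independent, the chance that both succeed is 0.8764 × 0.8856 = 0.776 with 6 per group and 0.9291 × 0.9357 = 0.869 with 7.

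Operated-leg lean mass has no effect size in the article. Over an assumed range, power with 7 per group is 0.93 (d = 2.0), 0.73 (1.5), 0.54 (1.2), 0.41 (1.0) and 0.28 (0.8).

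**The case against.** The strongest reply is that the article already ranks its outcomes informally. It sizes the trial on mass and strength for its first aim, lists them first in the analysis, fixes 24 weeks as the primary time point and treats the genes as mechanistic. On that reading the relevant figure is 9.75%, not 37.0%. This largely stands, which is why the two-outcome figure leads. It does not remove the problem: two equal outcomes at 0.05 each still exceed 5%.

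The nine-outcome figure also treats Lachman and pivot shift as full 5% tests. If they are binary with 7 against 7, the uncorrected χ² false-positive rate is only about 0.3% to 3.8% at event rates of 10% to 30%. Leaving both out gives 1 − 0.95⁷ = 30.2% if independent.

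It may also be said that region, device and leg are details that an article leaves to the full protocol or analysis plan, and that the objectives speak of lean mass in general, not of the leg. That is fair as far as it goes. The point here is the stated rule of 0.05 for every analysis, which a later document would have to replace and not merely fill in. Nor is the operated limb ignored: affected-leg strength, affected-knee stability and KOOS are all collected.

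Stronger readings are tempting but not supported:

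- A reader might count two devices and two legs as separate tests, reaching 8 tests (34%) or, with genes, 11 tests (43%). The article does not say that devices or legs are tested separately.
- A reader might multiply further by visits. The named primary time point answers that.
- A reader might conclude that whole-body lean mass is definitely the analysed variable, or that the trial would declare success on the uninjured leg. The word whole-body describes the scan, and no success rule is stated. The text permits these outcomes but does not prescribe them.
- A reader might estimate how little one leg contributes to total lean mass. The masses needed are not in the article.

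**Conclusion.** The concern holds in a limited form. The rule of 0.05 for everything, with no primary outcome, gives about 8% to 9.75% familywise error on the two sizing outcomes at 24 weeks. Over all nine named outcomes it gives 37.0% if independent, or about 18% to 33% at correlations of 0.8 to 0.3. These figures assume no effect on any outcome; the correlations are assumed, and the nine-outcome figures are upper values given the small-sample χ² tests. Separately, with no leg fixed for strength and no region named for lean mass, a significant result could reflect the drug's systemic action and not the operated limb. How large that second effect might be cannot be computed from the article. The change is worth making and does not call for a new design.

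**What to change.** Replace the single 0.05 rule in Statistical data analysis with the following:

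1. At the 24-week primary time point, test the two sizing outcomes in fixed sequence, each by ANCOVA adjusted for its value two weeks before surgery. DXA lean mass comes first at 0.05; affected-leg dynamometer strength follows at 0.05 only if the first is significant.
2. Report operated-leg lean mass, read regionally from the same DXA scans if they permit it, as the key supportive outcome. Require affected-leg evidence before claiming better recovery of the operated limb.
3. Report impedance, the unaffected leg, KOOS, TAS, laxity tests, genes and other visits with 95% confidence intervals and no claim of significance.

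The cost is wording plus a regional read-out of scans already planned. Fewer outcomes can be called significant, and strength cannot be claimed if lean mass fails.

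The sponsor may prefer operated-leg lean mass as the primary outcome. That is defensible, but it must then state that the Power analysis gives no effect size or power for it: 7 per group would have power 0.93 at d = 2.0 but 0.41 at d = 1.0.
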